## Abstract

**Background:**

Stroke Early Supported Discharge (ESD) is a service innovation that facilitates discharge from hospital and delivery of specialist rehabilitation in patients’ homes. There is currently widespread implementation of ESD services in many countries, driven by robust clinical trial evidence. In England, the type of ESD service patients receive on the ground is variable, and in some regions, ESD is still not offered at all. This protocol presents a study designed to investigate the mechanisms and outcomes of implementing ESD at scale in real-world conditions. This will help to establish which models of ESD are most effective and in what context.

**Methods:**

A realist evaluation approach composed of two interlinking work packages will be adopted to investigate how and why ESD works, for whom and in what circumstances. Work package 1 (WP1) will begin with a rapid evidence synthesis to formulate preliminary realist hypotheses. Quantitative analyses of historical prospective Sentinel Stroke National Audit Programme (SSNAP) data will be performed to evaluate service outcomes based on the degree to which evidence-based ESD has been implemented. Work package 2 (WP2) will involve the qualitative investigation of purposively selected case study sites featuring in WP1 and covering different regions in England. The perspectives of clinicians, managers, commissioners, and service users will be explored qualitatively. Cost implications of ESD models will be examined using a cost-consequence analysis. Cross-case comparisons and triangulation of the data sources from both work packages will be performed to test, revise, and refine initial programme theories and address research aims.

**Discussion:**

This study will investigate whether and how current large-scale implementation of ESD is achieving the outcomes suggested by the evidence base. The theory-driven evaluation approach will highlight key mechanisms and contextual conditions necessary to optimise outcomes and allow us to draw transferable lessons to inform the effective implementation and sustainability of ESD in clinical practice. In addition, the methodological framework will progress the theoretical understanding of implementation and evaluation of complex rehabilitation interventions in stroke care.

**Trial registration:**

ISRCTN: 15568163, registration date: 26 October 2018.

Contributions to the literature
Use of a realist evaluation framework with triangulation of quantitative and qualitative elements to investigate implementation of a complex intervention in a real world settingA methodological approach to investigate the dynamic nature between an intervention’s core components, actors delivering the intervention, and context to determine if trial-related outcomes of a complex intervention are realised in practiceUse of national audit data and multilevel modelling statistics to explore effectiveness of a community-based stroke intervention at a patient and service levelAnalysis and data interpretation plans designed to inform future service implementation, local service improvement, and national performance monitoring

## Background

Stroke is one of the main causes of adult disability, and there is strong research evidence to show that provision of stroke specialist rehabilitation enhances recovery [1, 2]. Service delivery models that offer home-based stroke rehabilitation have gained increasing interest particularly as healthcare services face the challenge of cost reduction and integrated care provision [3–5].

Stroke Early Supported Discharge (ESD) is a multidisciplinary team intervention that facilitates discharge from hospital and delivery of stroke specialist rehabilitation at home and at an intensity equivalent to that provided in an acute stroke unit. Cumulative evidence from clinical trials has shown that ESD can reduce the length of hospital stay and the risk of dependency of stroke survivors [6, 7]. As a result, there is currently widespread implementation of stroke ESD services in the UK and other countries.

In England, National Clinical Guidelines from the Royal College of Physicians and the National Institute for Health and Care Excellence (NICE) recommend the provision of ESD as part of an evidence-based stroke care pathway [2, 8]. Yet, despite these research and policy drivers, national audit reports showed that the type of ESD services stroke patients receive is variable, and in some regions, ESD is still not offered at all [9]. Alternative models of operation have been adopted, but it is not known how close they are to the evidence-based models with demonstrated effectiveness in clinical trial settings. It remains unclear whether health and cost benefits of the ESD intervention are achieved when services are implemented in practice. With outcome-based commissioning becoming a priority within the National Health Service (NHS) in the UK, it is important to investigate whether ESD services are still effective in real-life clinical settings. Distinguishing between effective and ineffective implementation is crucial to address inequities in service provision and plan service improvements [10]. It is also vital with regard to informing implementation of sustainable evidence-based service models.

Large-scale implementation ESD needs to be considered in the light of the complexity inherent in the delivery of this type of intervention. ESD is a multidisciplinary and multicomponent healthcare intervention that involves a critical mass of stakeholders working across different organisation settings along the stroke care pathway. It is acknowledged that successful community-based care requires not only a shift in budget investment from acute to community services but also dissolving traditional occupation and organisational boundaries [3, 11]. ESD services do not operate in the controlled environments of experimental settings but in a complex and multilevel system such as the NHS. They are, therefore, exposed to a range of contextual influences at different levels of the healthcare system which act synergistically or antagonistically to evidence-based implementation. Decoding the observed variability requires distinguishing between receptive and non-receptive contexts as well as understanding the interplay between these environments and the programme’s ‘active ingredients’ [12]. This process of enquiry permits a better understanding of why the programme works in certain settings and not in others, what mechanisms underlie the programme’s success, and what steps we need to make in order to achieve the desired outcomes. Findings can then inform future implementation, reconfiguration, and improvement of ESD services to facilitate provision of evidence-based stroke care.

This paper presents the protocol of a multimethod study investigating what, why, and how ESD services are implemented and operate in real-world settings. The study responds to the second translation gap between clinical trials and clinical practice with the view to facilitating further implementation of ESD nationally and internationally. We will draw upon realist evaluation principles to unpick the interplay between ESD services and the context within which they operate, determine whether and how they are effective and in what conditions [13]. The study objectives will be as follows:To investigate the effectiveness of ESD services when implemented at scale, in practice.To understand how the context within which they operate influences the implementation and effectiveness of ESD schemes.To identify transferrable lessons to drive effective implementation of stroke ESD in clinical practice.

To achieve these objectives, we will seek to answer the following questions:What adopted models of ESD exist and how do these relate to evidence-based recommendations?Can realised benefits of implementing ESD be quantified by defined measures of effectiveness: reduction in length of hospital stay, responsiveness of the service, amount of rehabilitation delivered, and changes in patient dependency?What site-, model-, and patient-level characteristics influence effectiveness of ESD services?What are the cost consequences of adopted ESD models?What contextual elements influence whether ESD is implemented in the first place and how do they shape the model of service adopted?What are the perceived outcomes of implementing ESD from the perspective of service users, clinicians, managers, and commissioners and how are these achieved in practice?What are the conditions that contribute to the successful implementation and sustainability of ESD in practice?

## Methodology

### Conceptual framework

To address our research questions, we will draw on a realist evaluation (RE) approach [13]. RE is a theory-driven research evaluation that attempts to unpack the black box between complex healthcare programmes and the generated outcomes. Healthcare programmes are perceived as the manifestation of explicit or implicit theories that embody the developers’ and implementers’ assumptions about how the programme works [13, 14]. The evaluation starts by eliciting these key theories and mapping them into context-mechanisms-outcomes (CMO) configurations. CMOs are essentially hypotheses that explain what works, for whom, under what circumstances and how. In the process of data collection, realist hypotheses are put to test, revised, and refined, leading to more sophisticated programme theories and a better understanding of how programmes achieve their outcomes and in what settings [15].

We will start our inquiry by surfacing the core ‘formal programme theory’ about how ESD schemes work, as advocated by the evidence base [13–16]. Our previous research and national clinical guidelines have shed light on the ‘active ingredients’ that make an ESD service effective by defining evidence-based core components; these are the proposed essential characteristics that theory suggests need to be implemented for the programme to work in clinical practice [17, 18]. Formulated as a CMO proposition, what this evidence suggests is that ‘In urban settings (context), coordinated, stroke specialist multidisciplinary ESD teams (mechanisms - resources) provide timely hospital discharge and intensive home rehabilitation (outcomes), reducing length of in-hospital stay and improving long-term functional outcomes (outcomes)’.

Articulated in RE terms, it becomes apparent that the formal theory only partially explains how and in what contexts the programme works. In addition to patient level factors (i.e. stroke severity), previous research suggests that contextual elements operating at the levels of the team and the organisation as well as features of location need to be considered as part of an investigation of ESD services [17–19]. This fits well with current implementation research frameworks which highlight the importance of considering the characteristics of context at meso- and macro-levels [12, 20]. Since ESD is delivered to patients in their own home, thus necessitating the delivery of rehabilitation over potentially large geographical areas, the influence of the geographical location within which the service operates also needs to be understood. The question of how ESD schemes might operate in rural settings has been raised, given the fact that most of the original trials were conducted in urban settings. What needs to be stressed, however, is that the mere description of context does not explain why a different context generates different outcomes [21]. Examining the interaction between contexts and programme mechanisms will also be required in order to understand how the conditions within which the programme works activate and shape these mechanisms.

Regarding the underlying mechanisms, formal theory implies a causal relationship between the core components of the intervention and its outcomes [12]. According to the realist understanding of causation, interventions cannot directly cause outcomes but they provide (or take away) resources [15]. Programme mechanisms are understood as an interaction between the opportunities offered by the interventions and stakeholders’ reasoning and responses to these resources. Realists’ definition of mechanisms highlights the importance of human reasoning and interpretation as vital to understanding how an intervention works [14]. Evidence suggests that the behaviour of individual ESD team members, particularly across organisational boundaries, might influence the adoption and delivery of ESD services [19]. This also resonates with current implementation theory, which acknowledges the importance of actors involved in implementation as well as the context in which they are operating [20].

To fulfil the study’s aim, the formal theory needs to be refined and preliminary realist hypotheses developed, codified into CMO conjectures, and tested through data collection. We drew on the work of Dalkin et al. [22] who suggested that explicitly disaggregating mechanisms into resources and responses highlights the difference between the intervention and generative mechanisms and facilitates the formulation of CMO configurations. We conceptualised the evidence-based core components of ESD services as the programme resources, and we will seek to surface the perspectives and behaviours of actors and stakeholders (staff and patients) who are making ESD happen on the ground. As intended outcomes, we used the process and patient outcomes examined by clinical trials and the national stroke audit, but we also allowed for exploration of unintended outcomes, mainly through the qualitative component of the study. Table 1 presents an initial CMO framework, which we will use to configure our realist hypotheses and examples of initial plausible scenarios. This example explores how the rurality of the location of the ESD service may lead to a facilitatory or countervailing interaction with mechanisms to generate intended or unintended outcomes. These hypotheses will be put to test through data collection and analysis in order to fine-tune underpinning CMO configurations and increase our understanding of how these elements are related [13]. This approach will be compared to existing implementation research frameworks, acknowledging the dynamic nature between an intervention’s core components, actors delivering the intervention, and the context in which this takes place [12, 20].

**Table 1 Tab1:** Programme theory CMO framework

Context	Mechanisms (resources + responses)		Outcomes
Rurality of ESD service location	Eligibility criteria		Accelerated transfer of care from hospital to home
	Team composition		
Commissioning and financial arrangements	Whole time equivalent staff/patient ratio	Staff perspectives/behaviour	Rehabilitation delivery—responsiveness
ESD provider organisation	Stroke specialism and staff training	Patient perspectives/behaviour	Rehabilitation delivery—intensity of rehabilitation
Referring services characteristics and locations	Multidisciplinary team co-ordination (e.g. meetings)		Patient outcomes—recovery

Example of a facilitatory CMO with intended consequences

‘If members of an ESD service have to cover long travelling distances in a rural setting, then the team may respond by making effective use of communication at team meetings and increased coordination (timetabling), resulting in patient centred goal setting and increased intensity of rehabilitation provided’

Example of a countervailing CMO with unintended consequences

‘If members of an ESD service have to cover long travelling distances in a rural setting, this may place a burden of the team’s communication and coordination and result in patients receiving less therapy than patients in urban settings’

### Study design

We will adopt a mixed methods design to draw information from multiple complementary sources. Our previous research and quantitative data analysis will inform mainly the ‘Context’, ‘Mechanisms-resources’ and ‘Intended Outcomes’ and qualitative data used to elicit ‘Mechanisms-responses’ and ‘Unintended outcomes’ [17–19]. The study will be conducted in two stages corresponding to two interlinking work packages undertaken sequentially (Fig. 1). Work package 1 (WP1) will begin with a literature review aiming to identify key contextual determinants to the implementation of ESD service and elicit potential mechanisms. Quantitative analyses of historical prospective Sentinel Stroke National Audit Programme (SSNAP) data will be then performed. The results from WP1 will complement but also feed into work package 2 (WP2) by informing the development of candidate realist programme theories formulated as CMO configurations which will then be tested, revised, and refined through WP2. Work package 2 will generate insights from the perspectives of actors and stakeholders who are making ESD happen in the real world. An exploratory multiple case study design will allow ESD sites featured in WP1 to be investigated qualitatively, drawing information from individual interviews, focus groups, and documentary evidence. A cost-consequence analysis will be performed to investigate the costs associated with ESD implementation drawing information from interviews and documentary evidence. Finally, data from each work package will be synthesised in order develop more sophisticated programme theories (with underpinning CMOs) that address the study’s questions.

**Fig. 1 Fig1:**
[figure not shown]
Flowchart of study including work packages 1 and 2

### Work package 1

#### Rapid evidence synthesis

Given that context is a ‘slippery’ notion, identifying the salient contextual conditions relevant to the operation of ESD services will be the first step towards developing realist hypotheses. A rapid evidence synthesis (RES) will be conducted to identify contextual features having the potential to facilitate or impede the implementation of services providing home-based stroke rehabilitation [23]. RES is gaining popularity as it provides a robust and pragmatic approach to conducting a literature review to address specific questions. Database searches will be carried out in the Medline (OVID), CINAHL, and Embase databases for articles published since January 2000. A mixed research synthesis approach will be used where both qualitative and quantitative studies will be considered for inclusion based on their relevance to our research question. To define and structure different types of contextual factors identified in the literature, we will draw on implementation research models of determinants [12, 20, 24]. For the purposes of this study, we are particularly interested in the influence of adoption of evidence core components and the rurality of ESD service location.

#### Site selection

This study is designed to investigate the impact of different models of ESD operating over defined geographical regions of the East Midlands, West Midlands, East of England, and North of England (clinical network boundaries). This will allow an investigation of the consequences of a Midlands and East initiative to implement ESD beginning in 2012 [25] contrasted with a region (North of England) that has been slower to implement ESD based on SSNAP post-acute organisational audit data [9]. Sites within each of the four regions will be defined according to Clinical Commissioning Group (CCG) and local authority boundaries. All individual ESD teams within each site that participate in the SSNAP clinical audit will be included.

#### Data collection and analysis

Work package 1 will involve analysis of historical prospectively collected SSNAP data from hospital and community providers across the East Midlands, West Midlands, East of England, and North of England strategic clinical networks. A key aim of WP1 is to investigate whether the degree to which an ESD service has adopted an evidence-based model is related to better patient care (measured by ESD responsiveness and rehabilitation delivered) and patient dependency (modified Rankin Scale) [26] as well as the influence of rurality of the ESD service location. Effects of ESD on length of hospital stay will also be investigated; however, this analysis will require a different calibration of the statistical model and will be dealt with separately. To conduct these analyses, we employ multilevel modelling as it is an appropriate technique when analysing outcome variables that are generated from a clustered/nested structure whereby the outcome under consideration is produced by patients in different ESD team/hospital settings.

The effectiveness of ESD will be measured with evidence-based metrics as defined by national clinical guidelines for stroke and that reflect outcome measures used in the original ESD trials [6, 7]. Measuring the effects that ESD teams have on their patients is a necessary first step to learning how ESD practices combine to generate differences between teams. Combining SSNAP clinical audit data at the patient level with post-acute organisational audit data at the ESD team level, we will attempt to measure the ‘true’ effects that ESD teams have on their patients by fitting two-level patients-within-teams multilevel models to patient and process outcomes where covariate adjustments are made for a range of patient and ESD team characteristics.

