#### Evaluating the effectiveness of ESD service provision

To investigate our study hypotheses, information about each ESD service collected by SSNAP in the 2015 post-acute organisational audit will be collated by the research team. This will include ESD team composition, capacity, workload, and organisational features, e.g. frequency of team meetings. ESD team models will then be analysed by comparing ESD service information with ESD consensus statements and national clinical guideline recommendations [2, 8, 17]. This will be the first step in the investigation of adoption of evidence-based core components, e.g. stroke specificity and multidisciplinary team composition. An ESD consensus score will be applied to each ESD team included in our multilevel modelling.

Additional variables in the model obtained from the 2016 SSNAP clinical data at the patient level will include age at admission, sex, pre-stroke independence, comorbidities, NIH Stroke Scale score on admission, type of stroke, and modified Rankin score at discharge from hospital [26, 27]. These reflect previously validated stroke case-mix models [28, 29]. Data variables at the ESD team level (in addition to the ESD consensus score) will include level of rurality and deprivation [30] as well as the grade/score of each discharging hospital as recorded by the SSNAP team (to account for the influence of the quality of inpatient care prior to ESD). A ‘team-size’ score will also be included (total whole time equivalent (WTE) units per member of staff). By including these ESD team-level ‘contextual variables’ in our analysis, we are assuming that they may not be homogeneous across the ESD teams and may impact upon service provision as well as patient outcomes. Moreover, multilevel modelling enables us to appreciate the variation in outcomes as a mixture of patient variability nested within ESD service provision variability. Effectiveness of ESD service provision will be measured with the following outcome variables: responsiveness (time from hospital discharge to first contact), rehabilitation intensity (total number of treatment days/total days with ESD), and stroke survivor outcome (modified Rankin Scale after ESD delivered).

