#### Cost-consequence analysis

Cost implications are likely to be an important consideration with regard to successful adoption and implementation of interventions such as ESD. Economic evaluation methods for complex interventions, such as ESD, should ideally consider the wider costs and benefits associated with the intervention. It has been argued that generic outcomes such as quality-adjusted life years (QALYs) may not be suitable to capture these wider effects [33]. In addition, standard cost-effectiveness measures have poor recognition of the importance of context, lacking interest in links between causal mechanisms and relevant contexts that are thought to produce expected outcomes. Resources associated with delivery of a complex intervention are likely to equate to different costs in different places [34].

Given these issues, a cost-consequence analysis will be deployed. This form of analysis has been recommended for complex interventions that have multiple effects as it offers a more flexible approach to presenting costs and benefits alongside each other rather than combing these into a single measure [33]. This approach also fits with the realist approach of the study, in that costs associated with ESD-related mechanisms will be considered in light of context in which they are operating and the outcomes or benefits that are achieved.

In order to obtain the cost data necessary for an analysis of this kind, contrasting ESD model types represented by the six teams selected for inclusion in work package 2 will be used. SSNAP post-acute organisational audit data will be supplemented by more detailed information gathered from teams directly (e.g. service specifications). Multidisciplinary team composition and workload (WTE) information will be used to calculate associated NHS costs. Staff training budgets will be considered (given the importance of stroke specific expertise). Travel costs associated with delivery of rehabilitation will be estimated by defining the geographical area over which the ESD service operates, determining average distances travelled and number of patient visits made. Using patient caseload information, direct costs per patient will also be calculated. Differences in length of hospital stay and changes in modified Rankin derived from the comparison of ESD model types will be used to estimate treatment effects.

#### Triangulation of findings from work packages 1 and 2

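### The modified Rankin model contains only ESD recipients, so the study cannot show whether ESD's dependency benefit is realised in practice; it can show only adjusted differences between ESD teams

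*Protocol article*

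**What the plan says.** Several places set a broad target:

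- The second research question, at the end of the Background, asks "Can realised benefits of implementing ESD be quantified by defined measures of effectiveness". Change in patient dependency is one of the four measures it lists.
- The Discussion part of the Abstract says the study will investigate "whether and how current large-scale implementation of ESD is achieving the outcomes suggested by the evidence base". The Background names lower risk of dependency, alongside shorter stay, as what the trials showed.
- The contributions list after the trial registration and the Impact section repeat the aim of finding out whether trial outcomes or benefits are realised in practice.

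The dependency analysis is described more narrowly:

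- On who is included, Site selection (Work package 1) says: "All individual ESD teams within each site that participate in the SSNAP clinical audit will be included".
- On the team-level exposure: "An ESD consensus score will be applied to each ESD team included in our multilevel modelling".
- The outcomes, besides time to first contact, are "rehabilitation intensity (total number of treatment days/total days with ESD), and stroke survivor outcome (modified Rankin Scale after ESD delivered".
- Data collection and analysis says the team models attempt to measure the 'true' "effects that ESD teams have on their patients by fitting two-level patients-within-teams multilevel models", adjusting for patient and team characteristics.

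A comparison with no ESD appears only under ESD impact on patient length of hospital stay, in the cross-sectional and the difference-in-difference analyses. There, patients are nested in admitting hospitals, a different dataset is used, and length of stay is the outcome.

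The Cost-consequence analysis adds that length-of-stay differences and "changes in modified Rankin derived from the comparison of ESD model types will be used to estimate treatment effects".

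**The concern.** The trial evidence on dependency is a contrast between ESD and no ESD. Asking whether that benefit is being realised at scale asks for the same contrast, or something standing in for it. The dependency model has no such contrast: a patient who did not receive ESD has no ESD team, no consensus score and no post-ESD modified Rankin value, so cannot enter it.

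What is at stake is the conclusion, not the fit. The article says its findings will inform commissioning. Improvement in modified Rankin between hospital discharge and the end of ESD could be presented as a realised benefit, although it mixes any effect of ESD with the recovery that would have happened anyway. Conversely, a flat relation between consensus score and modified Rankin could be taken to mean that ESD does not reduce dependency. It would show only that teams with higher and lower scores did not detectably differ.

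**Working it through.** The article gives no sample size, power or effect size on this point, and none is needed. The question is what the model can identify.

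**Inputs from the article.** Level 1: patients. Level 2: ESD teams. Team-level terms: consensus score, rurality, deprivation, discharging-hospital score, team size. Patient-level terms: case mix, including modified Rankin at hospital discharge. Outcome: modified Rankin after ESD.

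**Step 1: write the effect of ESD into the model.** For patient i of team j, with m the discharge modified Rankin and s the consensus score (other covariates omitted):

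y_ij = b0 + tau × ESD_ij + b1 × m_ij + b2 × s_j + u_j + e_ij

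Here tau is the average effect of ESD against no ESD, and b0 includes ordinary recovery over the period.

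**Step 2: apply the inclusion rule.** ESD_ij = 1 for every patient, so

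y_ij = (b0 + tau) + b1 × m_ij + b2 × s_j + u_j + e_ij

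The data determine the sum b0 + tau, never tau alone. More patients or teams make the sum more precise but do not split it. Adjusting for discharge modified Rankin does not help, because recovery and ESD still act together after discharge. If modified Rankin is modelled as ordinal, the thresholds absorb tau on the link scale in the same way. If the effect of ESD varies by team, the deviations from the average enter b2 and u_j, and the average stays in the intercept.

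**Step 3: numerical illustration.** Assumptions, none from the article: 30 teams of 100 patients, a continuous modified-Rankin-like outcome, a random-intercept model, and the same simulated data each time apart from the common effect tau.

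| tau | Intercept | Slope on discharge score | Consensus-score slope | Between-team variance | First three team residuals |
|---|---|---|---|---|---|
| 0 | 0.4764 | 0.7038 | -0.1278 | 0.0565 | 0.4227, -0.1675, 0.0522 |
| -0.3 | 0.1764 | 0.7038 | -0.1278 | 0.0565 | 0.4227, -0.1675, 0.0522 |
| -0.6 | -0.1236 | 0.7038 | -0.1278 | 0.0565 | 0.4227, -0.1675, 0.0522 |

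The intercept moves by exactly tau: 0.1764 - 0.4764 = -0.3, and -0.1236 - 0.4764 = -0.6. Nothing else changes. In real data the intercept without ESD is unknown, so the three situations could not be told apart.

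**Step 4: what is identified.** b2, the corresponding coefficients for rurality and the other team features, and the relative team effects u_j. These are contrasts between ESD teams, and they remain open to unmeasured differences in case mix.

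**The case against.** The strongest reply is that the article does not claim an average ESD effect from the team models. Much of this stands.

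- **Team effects.** A reader might infer that the 'true' effects in Data collection and analysis mean ESD against no ESD. The text does not support that. The word is in quotation marks, the sentence says attempt, and it goes on to describe covariate adjustment. The preceding paragraph states a between-team aim (degree of adoption, and rurality), and the preceding sentence speaks of learning how practices produce differences between teams. Case-mix-adjusted relative team effects is the natural reading.
- **Cost-consequence analysis.** A reader might infer that a benefit of ESD over no ESD is set beside the costs. The modified Rankin contrast there is already derived by comparing ESD model types; only the label 'treatment effects' is loose.
- **Process outcomes.** A reader might extend the point to responsiveness and intensity. As defined, neither has a meaningful counterpart without ESD, so the missing comparator does them no harm.
- **Pre-post estimate.** No section specifies an uncontrolled estimate of dependency benefit, or says one will be reported. Misreporting is a risk left open by the wording, not a planned step.
- **Separation of questions.** The article does keep length of stay apart, with its own comparator.

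What the reply does not reach is the second research question and the matching statements in the Abstract, the contributions list and the Impact section. These name realised benefits or trial outcomes without narrowing them for dependency. An analysis plan could not repair this, since the outcome is defined only for people who received ESD.

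**Conclusion.** The point holds for dependency only. The article promises to quantify, or to determine the presence of, a realised benefit that by its own account of the trials includes lower dependency. Its modified Rankin model cannot deliver this at any sample size: no benefit and a large benefit give the same score slope, team variance and team residuals. This rests on the inclusion rule and outcome definition as written; the simulated figures only illustrate the algebra.

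The key aim of relating adoption of the evidence-based model and rurality to outcomes does not depend on a no-ESD group and is left intact. The responsiveness, intensity and length-of-stay analyses are not affected. The wording on team effects and in the cost-consequence section needs clarifying and is not in itself an error. The change is worth making because it alters what the study may conclude, and it costs little.

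**What to change.** 1. In the second research question, with matching edits to the Abstract's Discussion, the contributions list and the Impact section, restrict the dependency target to case-mix-adjusted differences in modified Rankin between ESD teams, by degree of adoption of the evidence-based model and by rurality.
2. State that length of stay is the only outcome for which ESD is tested against no ESD.
3. State that neither modified Rankin change during ESD nor a null consensus-score slope will be reported as evidence for or against a benefit of ESD itself. Change during ESD may be shown descriptively.
4. In Data collection and analysis and in Cost-consequence analysis, clarify that 'true' effects and 'treatment effects' on modified Rankin mean between-team and between-model differences respectively.

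No model, dataset or outcome changes. The study gives up a claim about realised dependency benefit that it cannot support. Keeping that claim would need modified Rankin at a common time point in patients on pathways without ESD, a comparison the article does not describe.
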